### Study tools

Demographic profile: participants’ names, age, sex and other socioeconomic indicators will be recorded.Maslach Burnout Inventory (MBI) will be used to measure burnout. MBI is a 22-item survey that covers three areas: emotional exhaustion (EE), depersonalisation (DP) and personal accomplishment (PA) and uses a 7-point scale for responses. An answer can range from ‘never’ to ‘every day’. All three subscales show high internal consistency, with Cronbach’s α coefficients of 0.85, 0.76 and 0.71.^14^Salivary cortisol levels will be measured using the Human Cortisol ELISA Kit (Diagnostic Biochem, Canada). Saliva samples will be collected using the SpeciMAX Saliva Collection Kit at the start, middle and end of duty hours, before (day 0) and after (day 29) intervention. The samples will be centrifuged at 4000 rpm and stored at −20°C before analysis. For extraction, 100 µL of cortisol-HRP conjugate and wash buffer will be added to 50 µL of each sample. The plates will be shaken at room temperature for 45 min, washed and incubated with the TMB substrate for 15–20 min. The reaction will be stopped with the solution, and the absorbance will be measured at 450 nm using a microplate ELISA reader. Cortisol extraction will follow the method described by Kirschbaum *et al*.^15 16^Spielberger’s State-Trait Anxiety (STAI) Inventory will be used to measure state anxiety. STAI is a psychological inventory based on a 4-point Likert scale comprising 40 self-report questions. The STAI measures two types of anxiety—state anxiety, or anxiety about an event, and trait anxiety or anxiety as a personal characteristic. Higher scores are positively correlated with higher levels of anxiety.^17^ A high degree of internal consistency was observed for each of the 40 items, with Cronbach’s alpha value=0.38 to 0.89, while Cronbach’s alpha for the total scores is 0.86.^18^Six-letter cancellation test (SLCT) for the measurement of selective attention. The SLCT consists of a sheet of 22 rows×14 columns of randomly arranged alphabet letters. The top of each sheet names six target letters. Participants will choose two possible strategies to cancel target letters: (1) all six letters at once or (2) selecting a single target letter at a time. It also suggests that, according to their choice, they follow horizontal, vertical or random paths on the test sheet. They will be asked to cancel as many target letters as possible during a test time of 90. Different randomised arrays of letters on the worksheet are used to compensate for memory effects. SLCT test–retest reliability was found (r=0.781, p=0.002).^19^ This test is directly related to attention measurements. This test has been used in earlier studies on the Indian population.^20^,^22^ Therefore, this test was validated in this study.The self-rated scale of happiness will be used to measure happiness. A single self-rating scale will be used to assess happiness based on the question: ‘Do you feel happy in general?’. Following this question, a series of numbers from 0 to 10 will be written horizontally on one line with equal intervals. The research participants will be instructed: (a) imagine their global estimation and general feelings (not their present states), (b) take note that 0 is the minimum, 10 is the maximum score and (c) circle a number that best seems to describe their feelings. The 1-week test–retest reliability of the single-item self-rated happiness scale is 0.86.^23^

### Adverse events

The Institutional Ethics Committee (IEC) will be informed of any unexpected or serious adverse events within 48 hours of their occurrence. If any unexpected or serious adverse event occurs, participants will be provided medical treatment immediately.

### Analysis of outcomes

Intention-to-treat (ITT) and per-protocol analyses will be performed to provide a comprehensive understanding of intervention effects. The proportions and means will be calculated for descriptive analysis. The normality of the data will be checked using the Shapiro-Wilk test. Continuous data will be reported as mean±SD and compared using an independent t-test. Categorical data will be reported as frequencies and compared using the χ^2^ test. An independent t-test will compare pre and postintervention data of all group outcomes. A paired t-test will be used to compare the pre and postdata of all outcomes within the group. Statisticians will be blinded to group assignments for statistical analysis. Statistical calculations will be performed by SPSS V.26.0.

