### Sample size

A sample size of 108 with 54 subjects in each arm (attrition rate 15%) is calculated based on an assumed effect size of 0.60 and with a type 1 error (α) of 0.05 and power (β) of 0.80, using the G Power software.^12^

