### Randomisation

After baseline assessments, participants will be randomly assigned in a 1:1 ratio to either the yoga group (20 min yoga) or the control group (20 min medium-paced walking). A random number sequence will be generated using a computer-generated programme in Microsoft Excel. The allocation sequence will be concealed in sequentially numbered, opaque, sealed envelopes. The corresponding author will generate random numbers and allocate sequences in opaque sealed envelopes.

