### Outcomes

The primary outcome of this study is to compare the changes in burnout among healthcare workers after the daily practice of a 20 min yoga module to walking for a similar duration for 4 weeks. Secondary outcomes are changes in stress levels, anxiety, selective attention, and happiness scores among healthcare workers after the same 4-week intervention.

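### The between-arm test is unadjusted and does not say whether post scores or changes are compared; an ANCOVA on the baseline already collected would be clearer and probably more precise

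*Protocol article*

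**What the plan says.** The Outcomes section states: "The primary outcome of this study is to compare the changes in burnout among healthcare workers", with yoga set against walking over 4 weeks. Table 1 places the Maslach Burnout Inventory (MBI) at baseline and at day 29, so every analysed participant should have a baseline burnout score.

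The Analysis of outcomes section gives two tests. Between arms: "An independent t-test will compare pre and postintervention data of all group outcomes". Within arms: "A paired t-test will be used to compare the pre and postdata of all outcomes within the group". It names no covariate, and does not say whether the between-arm test is on day-29 scores or on day-29 minus day-0 differences.

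The Sample size section says that the number was "calculated based on an assumed effect size of 0.60", "with a type 1 error (α) of 0.05 and power (β) of 0.80". It does not name the outcome or the scale (post score or change) to which 0.60 refers.

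**The concern.** The primary question is whether burnout changes more under yoga than under walking. The test sentence can be read as two separate comparisons, one of pre means and one of post means. The pilot was reported that way: Table 4 gives between-arm p-values at day 0 and at day 29, and tests change only within each arm. The pilot text then sets a significant yoga arm against a non-significant control arm and concludes that the intervention improved burnout, although the day-29 between-arm p-values are 0.705 (emotional exhaustion, EE), 0.423 (depersonalisation, DP) and 0.506 (personal accomplishment, PA). A contrast between two within-arm p-values is not a test of the difference between arms, and the main trial keeps the same pair of tests.

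If the main trial does compare post scores, stable differences between people stay in the error term although the baseline that would remove them is in hand. At stake are precision on the primary outcome and a choice left open among post-score, change-score and within-arm results.

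**Working it through.** **1. The plan's own sample size.** Two-sample t-test (noncentral t), two-sided α 0.05 (sidedness is not stated, so this is assumed), d=0.60, power 0.80: 45 per arm. Allowing for 15% attrition, 45/0.85 = 52.9, so 53 per arm and 106 in total, within 2 of the stated 108. With 54 × 0.85 = 45.9, about 46 analysable per arm, power is 81%. The figure is reproduced.

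**2. Pre-post correlations from Table 4.** Inputs: means, SDs and paired p-values, with n=9 (yoga) and n=8 (control) completers.
- t = t quantile at 1 − p/2 on n−1 df
- SD_change = |mean change| × √n / t
- r = (SD0² + SD1² − SD_change²) / (2 × SD0 × SD1)

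| Subscale, arm | Change | Paired p | t | SD_change | r |
|---|---|---|---|---|---|
| EE, yoga | 24.67 − 19.44 = 5.23 | 0.009 | 3.43 | 4.58 | 0.79 |
| EE, control | 22.75 − 21 = 1.75 | 0.31 | 1.09 | 4.52 | 0.87 |
| PA, yoga | 29.56 − 26.56 = 3.00 | 0.037 | 2.50 | 3.60 | 0.91 |
| PA, control | 26 − 24.5 = 1.50 | 0.683 | 0.43 | 9.96 | 0.69 |

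The pilot text gives 0.03 instead of 0.037 for PA in the yoga arm; that moves r only from 0.91 to 0.92. For cortisol the reported change SDs (21.96 and 26.43) give r=0.52 and 0.40 directly. DP was tested by Wilcoxon, so no r can be derived.

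**3. Variance relative to a post-only t-test.** ANCOVA leaves 1 − r². Intervals use Fisher's z with SE 1/√(6+5) = 0.30.

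| Outcome | Pooled r (approx. 95% CI) | 1 − r² | Reduction |
|---|---|---|---|
| EE | 0.84 (0.56 to 0.95) | 0.30 | 70% (31% to 90%) |
| PA | 0.76 (0.39 to 0.92) | 0.42 | 58% (15% to 85%) |
| Cortisol | 0.46 (−0.10 to 0.79) | 0.79 | 21% |

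**4. The pilot's EE contrast, three ways.**
- Post-only: 19.44 − 21 = −1.56. Pooled SD 8.13, SE = 8.13 × √(1/9 + 1/8) = 3.95, t = −0.39, p = 0.70 (Table 4: 0.705).
- Change: −5.23 − (−1.75) = −3.48, SE 2.21, t = −1.57, p = 0.14.
- ANCOVA (pooled slope 0.86): −1.56 − 0.86 × (24.67 − 22.75) = −3.21, SE 2.24, t = −1.43, p = 0.17.

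Adjustment nearly halves the standard error. None of the three is significant with 17 people.

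**5. Power for a 3.48-point EE difference.** This borrows the imprecise pilot estimate for illustration only: 3.48/8.13 = 0.43 SD, 46 per arm, two-sided 0.05. The effective d is divided by √(2(1 − r)) for change scores (equal SDs) and by √(1 − r²) for ANCOVA.

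| r | Post-only | Change score | ANCOVA |
|---|---|---|---|
| 0.5 | 53% | 53% | 65% |
| 0.8 | 53% | 89% | 92% |

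At the lower EE limit, r=0.56, ANCOVA gives 69%.

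**6. If changes were meant.** The change-score variance is already 0.31 (EE) and 0.49 (PA) of post-only. ANCOVA at 0.30 and 0.42 then removes only about a further 6% and 13%.

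**The case against.** The strongest reply is that the test sentence does not exclude a t-test on changes, and the Outcomes section speaks of changes. A reader might infer from Table 4 that the main trial will never test change between arms. The documents do not establish that: Table 4 shows how a small pilot was reported and supports the post-score reading without settling it. On the change-score reading, step 6 shows that little precision is lost at high r. This stands, and it is why unclear wording is part of the defect.

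Other stronger readings also fail:
- **That the test is biased by baseline imbalance.** Under the 1:1 randomisation, the unadjusted t-test is unbiased with correct type I error, and chance imbalance is reflected in its standard error. At d=0.60 it has the power that was planned.
- **That most of the precision is lost on every outcome.** This holds, as a point estimate, for EE and PA on the post-score reading only. It does not hold for cortisol and cannot be checked for DP.
- **That a benefit of the pilot's size would probably be missed.** Post-only power is 53%, so detection is slightly more likely than not.
- **That the sample size is conservative under ANCOVA.** The scale of the 0.60 is not stated. If it refers to changes, ANCOVA lifts power only from 81% to 85% at r=0.8.
- **That normality checking will switch the main trial's tests.** The main plan mentions a Shapiro-Wilk check but names no alternative test; rank tests are described for the pilot only.

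None of this defends leaving the comparison undefined or the baseline unused.

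**Conclusion.** The point holds as one of clarity and efficiency, and should be fixed. The plan commits to an unadjusted between-arm test, does not say which quantity it tests, and leaves usable baseline information out of the model.

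The likely size depends on two things the documents do not fix. The first is the reading: the loss is large if post scores are compared and small at high r if changes are. The second is the correlation: the values come from 9 and 8 completers, back-calculated from rounded p-values, with wide intervals. ANCOVA does at least about as well as either alternative over the range considered (r from 0.5 to 0.8), so the recommendation does not depend on the pilot values being right. The result does not make the planned test invalid or the trial underpowered at its stated effect size.

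**What to change.** Recruitment was still ongoing when the article was written, so the wording can be settled before analysis. Replace the between-arm sentence with text such as:

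*For each MBI subscale, the arms will be compared by ANCOVA of the day-29 score with arm as factor and the day-0 score as covariate. The treatment effect is the adjusted mean difference with its 95% confidence interval; robust standard errors or a bootstrap interval will be used if residuals are skewed. Within-arm paired tests are descriptive and will not be used to infer a difference between arms.*

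Apply the same model to the secondary outcomes, naming each baseline: day-0 happiness; for cortisol, which is sampled three times per duty day, one named summary used at both day 0 and day 29; and for the STAI and the six-letter cancellation test, the day-1 pre-session score, if sessions are bracketed by readings as in the pilot. The day-28 reading to be analysed for those two should be named as well.

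State in the Sample size section which outcome and scale the 0.60 refers to, and do not add a claim that the number is conservative.

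The cost is a change of wording and one degree of freedom, negligible with about 92 analysable participants. The model runs in the planned software on data already scheduled and needs no extra participants.

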## Abstract

Burnout among healthcare workers is a significant global concern that affects their well-being and professional efficacy. Yoga has shown promise in reducing burnout and improving mental health outcomes. However, due to their hectic schedules, healthcare workers often struggle to find time for self-care. A 20 min yoga module has been developed specifically for them to address this. So, this study aims to assess the efficacy of a specific 20 min yoga module in reducing burnout among healthcare workers. An open-label, two-arm, randomised controlled trial involving healthcare workers aged 20–35 years participating for 4 weeks. Exclusion criteria included recent illness, respiratory ailments, pregnancy, life-threatening medical conditions or physical inability to perform yoga. After randomisation of 108 participants, they will be equally allocated to either the yoga group (20 min yoga) or the control group (20 min medium-paced walking). The primary outcome will be burnout, whereas the secondary outcomes include stress, anxiety, selective attention and happiness. Data collection: at baseline and after 4 weeks of intervention, compliance is monitored via daily attendance records. Descriptive and inferential analyses will employ intention-to-treat and per-protocol analysis using SPSS 26.0. A study with 20 participants found that a 20 min yoga intervention significantly improved emotional exhaustion, depersonalisation, personal accomplishment, happiness and Spielberger’s State-Trait Anxiety/Six-letter cancellation test scores. Cortisol levels showed trends of reduction but were not significant. These results inform the upcoming main trial. Ethical approval is obtained from the Institutional Ethical Committee via letter number AIIMS/IEC/20/762. The trial findings will be shared through peer-reviewed publications and presentations at conferences. Trial registration number: CTRI/2021/01/030568; Clinical Trial Registry of India.

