## Results of the pilot study

A pilot study was conducted to evaluate the feasibility of an intervention. The quality of practice was assessed using a 10-point Likert visual analogue scale, with participants achieving an average mean score of 9 out of 10. This high score indicates strong acceptability among participants, demonstrating their comfort and ability to perform the practices included in the yoga module effectively.

A total of 20 participants were recruited for the pilot study, and informed consent was obtained from each participant. The participants, with a mean age of 31.6±5.3 years, were randomly assigned to either the yoga group (20 min yoga session) or the control group (20 min medium-paced walking). The interventions were delivered in offline classes and conducted at least 5 days a week over 4 consecutive weeks. Burnout scores were measured using the MBI, salivary cortisol levels were assessed with the ELISA technique and happiness scores were assessed using a self-rated happiness scale at baseline and after the 4-week intervention. State anxiety and selective attention were assessed using the STAI and SLCT, respectively, before and after the 20 min intervention at both baseline and after the 4 week intervention. Normality was checked with the Shapiro-Wilk test. Paired and independent t-tests were used for normally distributed data, while the Wilcoxon Signed Rank and Mann-Whitney U tests were used for non-normally distributed data.

Seventeen participants (nine from the yoga group and eight from the control group) completed the intervention. Statistical tests revealed a statistically significant improvement in scores in all the domains of burnout in the yoga group compared with baseline, as shown in table 4. Significant changes were found in EE (p=0.009), DP (p=0.028), and PA (p=0.03) in the yoga group. In contrast, no significant changes were observed in the control group across these domains: EE (p=0.31), DP (p=0.28), and PA (p=0.68).

**Table 4 T4:** Pre and postmean scores of MBI, salivary cortisol, happiness scale, STAI and SLCT in healthcare workers after 4 weeks of intervention

			Yoga group	Control group	P value
MBI					
Emotional exhaustion	Day 0	Pre	24.67±7.05	22.75±8.81	0.631*
	Day 29	Post	19.44±7.09	21±9.18	0.705*
		P value	0.009†	0.31†	
Depersonalisation	Day 0	Pre	7±5.72	5.5±2.98	0.481‡
	Day 29	Post	4.33±3.77	4±3.42	0.423‡
		P value	0.028§	0.324§	
Personal accomplishment	Day 0	Pre	26.56±8.08	24.5±12.92	0.705*

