	Day 29	Post	29.56±8.68	26±12.2	0.506*
		P value	0.037†	0.683†	
Salivary cortisol					
Concentration (ng/mL)	Day 0	Pre	77.89±17.5	71±20.97	0.477*
	Day 29	Post	63.11±25.07	64.13±26.58	0.937*
		P value	0.078†	0.486†	
Happiness scale					
Scores	Day 0	Pre	7.5±1.04	7.8±0.8	0.579*
	Day 29	Post	8.5±1.04	8±1.2	0.218*
		P value	0.007†	0.197†	
STAI					
Scores	Day 1	Pre	35.89±4.05	34.59±3.14	0.469*
		Post	32.66±3.16	34.76±3.33	0.205*
		P value	0.071†	0.922†	
	Day 28	Pre	38.79±5.23	32.04±7.25	0.049*
		Post	30.9±3.28	29.51±5.92	0.566*
		P value	0.017†	0.154†	
SLCT					
Scores	Day 1	Pre	25.89±6.58	26.54±4.89	0.82*
		Post	31.78±7.55	25.06±2.62	0.031*
		P value	0.021†	0.418†	
	Day 28	Pre	32.78±7.6	28.88±8.51	0.338*
		Post	38.67±9.49	30.38±6.95	0.057*
		P value	0.001†	0.255†	

P < 0.05 considered statistically significant.

* Independent t test.

† Paired t test.

‡ Mann-Whitney U test.

§ Wilcoxon Signed Rank Test.

MBI, Maslach Burnout Inventory; SLCT, Six Letter Cancellation Test; STAI, State Trait Anxiety Inventory.

The yoga group showed a trend towards reduced salivary cortisol levels (14.78±21.96 ng/mL), but this change did not reach statistical significance (p=0.078). The control group experienced a smaller decrease in salivary cortisol levels (6.87±26.43 ng/mL), which also did not reach statistical significance (p=0.48), as shown in table 4. Additionally, the yoga group had a significant (p=0.007) increase in happiness scores. Mean pre–post scores of the happiness scale are shown in table 4.

Significant changes were observed in the yoga group across both STAI and SLCT scores following the intervention. On day 1, while the Yoga group showed a non-significant (p=0.071) decrease in STAI scores, there was a significant (p=0.021) improvement in SLCT scores. On day 28, while the Yoga group showed a significant reduction in STAI scores (p=0.017), there was a substantial improvement in SLCT scores (p=0.001). In contrast, the control group showed no significant changes in either STAI or SLCT scores at any time. The mean scores of STAI and SLCT on day 1 and day 28, immediately before and after the intervention, are shown in table 4.

In conclusion, the 20 min yoga intervention significantly improved burnout scores, particularly in EE, DP and PA. While trends towards reduced salivary cortisol levels were noted in the yoga group, these findings did not reach statistical significance. These results will inform the main trial that follows.

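### The plan does not say which test decides efficacy, and the pilot drew its burnout conclusion from within-arm tests that its own between-arm results do not support

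*Protocol article*

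**What the plan says.** The Outcomes section makes the primary question comparative: to "compare the changes in burnout among healthcare workers after the daily practice of a 20 min yoga module to walking for a similar duration".

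The Analysis of outcomes section plans two families of tests. Between arms: "An independent t-test will compare pre and postintervention data of all group outcomes". Within each arm: "A paired t-test will be used to compare the pre and postdata of all outcomes within the group". It does not say which family carries the efficacy conclusion.

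The Results of the pilot study section shows how the two were weighed when both were available. It reports significant changes from baseline in the yoga arm for emotional exhaustion (EE), depersonalisation (DP) and personal accomplishment (PA), and continues: "In contrast, no significant changes were observed in the control group across these domains". It ends: "In conclusion, the 20 min yoga intervention significantly improved burnout scores, particularly in EE, DP and PA". The Abstract reports that the pilot "found that a 20 min yoga intervention significantly improved emotional exhaustion, depersonalisation, personal accomplishment, happiness" and other scores. The between-arm burnout p-values are printed in Table 4 but are not mentioned in the text. The pilot section closes by saying that its results will inform the main trial.

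**The concern.** A significant change in one arm and a non-significant change in the other do not show that the arms differ. The two paired tests ask whether each arm moved from its own baseline. Neither asks whether yoga moved more than walking, which is the trial's question. Regression to the mean, retest effects and any benefit common to both activities all enter a within-arm change.

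Equal improvement in both arms is a realistic case here. The Control group section presents walking as itself an intervention against burnout, and all three burnout means moved favourably in the pilot's walking arm (EE 22.75 to 21, DP 5.5 to 4, PA 24.5 to 26). At stake are the accuracy of the pilot claim as it now stands, and the error rate of the main trial if its results are read in the same way.

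**Working it through.** **1. Which test the trial was sized for.** Inputs (Sample size section): "assumed effect size of 0.60 and with a type 1 error (α) of 0.05 and power (β) of 0.80", 54 per arm, 15% attrition. A two-sided two-sample t-test at d = 0.60 needs 45 per arm. Allowing for attrition, 45 / (1 − 0.15) = 52.9, so 53 per arm and 106 in total, against 108 stated. A one-sided test needs 35, then 42 per arm, and does not fit. The size therefore fits a two-sided between-arm test.

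**2. Pilot, between-arm tests on day-29 scores.** Inputs: Table 4 means and SDs, n = 9 (yoga) and n = 8 (walking).

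| Domain | Yoga | Walking | p in Table 4 | p recomputed (Welch) |
|---|---|---|---|---|
| EE | 19.44 ± 7.09 | 21 ± 9.18 | 0.705 | 0.704 |
| DP | 4.33 ± 3.77 | 4 ± 3.42 | 0.423 (Mann-Whitney) | 0.85 (t-test, not comparable) |
| PA | 29.56 ± 8.68 | 26 ± 12.2 | 0.506 | 0.506 |

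**3. Pilot, between-arm tests on change.** Comparing post scores alone ignores baseline, so I also reconstructed the comparison of changes. The SD of change follows from the paired p-value: SD = |mean change| × √n / t, where t is the two-sided quantile for that p on n − 1 df.

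- EE yoga: change 19.44 − 24.67 = −5.23; p = 0.009 on 8 df; SD 4.58.
- EE walking: change 21 − 22.75 = −1.75; p = 0.31 on 7 df; SD 4.52.
- EE difference: −5.23 − (−1.75) = −3.48. Pooled SD = √[(8 × 4.58² + 7 × 4.52²) / 15] = 4.55; SE = 4.55 × √(1/9 + 1/8) = 2.21; t = −1.57; p = 0.14; 95% CI −8.2 to 1.2.
- PA: 3.0 (SD 3.60) against 1.5 (SD 9.96). Difference 1.5, t = 0.42, p = 0.68, 95% CI −6.1 to 9.1.
- DP: about −1.2, 95% CI −4.8 to 2.5, p about 0.5. This is approximate because its within-arm p-values come from a Wilcoxon test.

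No burnout domain shows a between-arm difference on either scale, and the intervals are wide.

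**4. What the pilot's reasoning would do in the main trial.** Let dz be the true mean change divided by the SD of change, equal in both arms, so that the true arm difference is zero. The documents give no dz for the main trial, so this is an assumption and a range is shown. With n = 45 completers per arm, P = Pr{noncentral t(44 df, dz√45) > upper 2.5% point of t(44 df)} is the chance that yoga alone is significant in the favourable direction. The arms are independent, so the pilot's contrast (yoga significant, walking not) has chance P × (1 − P).

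| dz | Yoga significant | Yoga significant, walking not |
|---|---|---|
| 0.1 | 10% | 9% |
| 0.2 | 26% | 19% |
| 0.3 | 50% | 25% |
| 0.4 | 75% | 19% |
| 0.5 | 91% | 9% |
| 0.6 | 98% | 2% |

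The contrast peaks at dz 0.3, where 0.503 × 0.497 = 0.25. In 20,000 simulated trials at each of three dz values, the between-arm t-test on change kept its two-sided error at 4.8% to 5.1%, so about 2.5% in favour of yoga. For scale, the pilot EE values correspond to dz of about 1.14 (yoga) and 0.39 (walking).

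**The case against.** A reader might infer that the main trial is set to decide efficacy by paired tests, that a false conclusion will follow, or that the walking arm serves no purpose. The documents do not support this. A between-arm test is planned for all outcomes, the primary outcome is worded as a comparison with walking, and the sample size fits a between-arm test. No sentence makes the paired test the criterion. Listing paired tests as description is no error. The article is condensed, and the ranking of tests may be left to an analysis plan that is not shown.

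A reader might also infer that the pilot showed yoga to be no better than walking. It did not: 17 completers leave wide intervals, and the absence of between-arm significance concerns burnout. Selective attention after the first session did differ between arms (p = 0.031).

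In the pilot's favour, its stated purpose was feasibility, its first sentence on burnout says the improvement is relative to baseline, and Table 4 prints the between-arm p-values. The 25% is the peak of an assumed range. A between-arm test would not remove differing expectations in an open-label trial, and the varied letter arrays already address part of the retest effect in the attention test.

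All of this limits the point without removing it. The pilot conclusion and the Abstract drop the reference to baseline and state an effect of the intervention, resting on a contrast of separate p-values. That is a misstatement in the current text, not a missing detail. The pilot also had both kinds of test and concluded from the within-arm ones, so leaving the deciding test open carries a demonstrated risk.

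**Conclusion.** The point holds in two parts.

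First, the pilot's claim of a significant effect on burnout is not supported by its own between-arm results, whether on day-29 scores or on the reconstructed EE and PA changes. The reconstruction assumes that the printed p-values are paired t-tests on the 9 and 8 completers. The text and Table 4 differ slightly on two within-arm p-values (DP walking 0.28 against 0.324; PA yoga 0.03 against 0.037), which does not alter the conclusion.

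Second, the main-trial section leaves open which test decides. Reading it as the pilot was read could wrongly favour yoga in about 2% to 25% of trials by the yoga-only contrast, or about 10% to 98% if the yoga arm were judged alone, against about 2.5% by the between-arm test. These figures are per outcome and assume equal true improvement of dz 0.1 to 0.6 and 45 completers per arm. They describe a risk that depends on how the results are read, not an expected result of the plan.

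**What to change.** 1. In Analysis of outcomes, replace the paired-test sentence with wording such as: Within-arm changes will be described as mean change with 95% confidence interval, and no efficacy conclusion will be drawn from them. The efficacy conclusion rests solely on the between-arm difference in post-intervention score, adjusted for the baseline score (ANCOVA).

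   An unadjusted between-arm test of change would also cure the inference problem. ANCOVA is preferred because it answers the comparative question in the Outcomes section and uses the baseline burnout score already collected before randomisation. In the pilot, yoga began 24.67 − 22.75 = 1.92 points higher on EE and ended 21 − 19.44 = 1.56 points lower, so a comparison of post scores alone and a comparison of changes (1.92 + 1.56 = 3.48) give different pictures.

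2. In the Abstract and in Results of the pilot study, say that burnout scores improved from baseline within the yoga arm and that no between-arm burnout difference was shown at day 29 (p = 0.705, 0.423 and 0.506). Remove the contrast between the arms' separate p-values.

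The first item changes the stated analysis method. Recruitment is reported as ongoing, so it should be recorded as a dated amendment before the data are analysed. The cost is that short amendment and a less favourable pilot statement; sample size and data collection are unaffected.
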